**Figure 1. f1:**
[figure not shown]
Study design and participant flow.

### Sample size

Study sample size calculation was conducted in G* Power (version 3.1). Based on previous study findings
^
36
^, 15 participants per group are required to detect a mean difference of 3.7 seconds in time to complete TUG with 80% power and significance at p<0.05. Additionally, based on the same findings
^
36
^, 16 participants per group will be needed to detect a mean difference of 1.52 in MNA-FF score between the intervention group and the control group with 80% power and significance at p<0.05. To ensure an adequate sample size to enable per protocol analysis, the sample size was increased to 23 participants per group
^
46
^. This will allow for both intention-to-treat and per-protocol analyses, ensuring rigorous analysis of intervention effectiveness.

### Eligibility criteria, recruitment and screening

Older adults who are ≥70 years old, community-dwelling and receiving regular supportive home care from a professional and/or informal carer
^
47
^ will be invited to take part in the research study. A variety of recruitment techniques will be employed including contacting home care associations, media coverage, poster distributions and face-to-face strategies such as presenting at community centres, day centres and exhibition shows for older adults. Non-profit organisations and charities that support older adults will also be contacted and asked to share information about the study. The inclusion and exclusion criteria are summarised in
Table 1. Individuals will be screened for eligibility using two screening questionnaires conducted via telephone: i) SARC-F questionnaire with a cut-off score of ≥1 (out of 10) to screen for risk of sarcopenia
^
48
^ (
Table 1) and ii) the Physical Activity for Readiness Questionnaire for Everyone (PARQ+) to assess participants’ readiness to participate in exercise. Older adults with moderate to severe cognitive (MMSE <24) impairment will be excluded due to the need for older adults to follow instructions independently at home to deliver an effective exercise dose and our concern about potential risk of injury given the online delivery of the resistance training programme.

**Table 1. T1:** Inclusion and exclusion criteria for the POWER Study.

Inclusion Criteria	Exclusion Criteria
1. Older adults (70+ years) 2. Community-dwelling 3. Receiving supportive home care (professional and/or informal) 4. At risk of sarcopenia (SARC-F ≥1) ^ 48 ^	1. Cognitive impairment (MMSE <24) ^ 53 ^ 2. Severe kidney disease (glomerular filtration rate <30 mL/min) 3. Moderate to severe liver disease (Child-Pugh class B or C) 4. Psychiatric disorder 5. Receiving active treatment or palliative care for cancer 6. Receiving enteral or parenteral nutrition 7. Allergic to dairy products 8. Known hypersensitivity to any component of the ONS 9. Currently consuming ONS 10. Regularly undertaking resistance training 11. Advised by GP not to undertake exercise

### Randomisation and blinding

On meeting the eligibility criteria, participants will be randomised into either the (i) ONS + RT or (ii) RT only, using a 1:1 ratio by an independent researcher not involved in the POWER study using the Clinical Trial Randomization Tool hosted by the
National Cancer Institute. Eligible participants will be assigned an identification number and then added to the study database. It will not be possible to blind the participant or researchers to the intervention allocation.

### Interventions

**
*Oral Nutritional Supplements*
**

Participants randomised to ONS + RT will consume two 200 mL bottles of whey-based protein ONS enriched with the amino acid leucine and vitamin D each day
^
49
^. On exercise days, the first ONS will be consumed at the time of day when the least amount of protein is normally consumed and the second ONS will be consumed as soon as possible after the RT session. On non-exercise days, the most appropriate time for consumption to optimise potential muscle protein synthesis will be based on a 24-hour dietary recall, undertaken at the baseline assessment
^
50
^. The nutritional content of the ONS (Fortimel Advanced, Nutricia) per 200 mL includes: energy: 300 kcal; protein: 20.8 g; leucine: 3 g; fat: 10.4 g; carbohydrate: 30 g; dietary fibre: 2.8 g; vitamin D: 10 µg (Appendix B)
^
45
^.

**
*Dietary advice*
**

All participants and home support person, if required, will be provided with written dietary information (“
Making the Most of Every Bite”, a high energy and protein cookbook, available from the Irish Health Service Executive). Additional dietary advice will verbally be provided to describe protein sources, portion sizes, timings and distribution of protein intake.

**
*Online resistance training programme*
**

A 12-week, progressive, group RT programme, developed with a registered physiotherapist and an exercise physiologist, will be delivered to all participants in their own home via Zoom twice per week by a health science researcher with exercise training (Exercise Instructor). Each RT session will last approximately 45–60 minutes, will include a warm-up and cool-down and moderate to high intensity RT exercises rated on the 10 point Borg Rating of Perceived Exertion (RPE) scale
^
51
^. During the baseline assessment, the exercises will be demonstrated, and the appropriate RT load will be determined using the 5- Repetition Maximum method
^
52
^.

The RT programme will include upper and lower body strengthening exercises, which can be modified to each participant’s muscle function, aiming for 2–3 sets of 8–12 repetitions. Exercises include sit-to-stand, shoulder press, bicep curl, calf raise, leg extension and lateral arm raise. Throughout the sessions, the exercise conducted, weight lifted during the exercise, sets and repetitions performed and RPE will be recorded (
Table 2). Following the T2 post-intervention assessment, participants will not receive the online RT programme. At the T2 assessment, they will be encouraged to continue to exercise but no additional supervised sessions or support will be provided between T2 and T3.

**Table 2. T2:** Progression plan from week 1 to 12 for the resistance training programme (2 sessions/week).

Phase	Week	Intensity	Duration	Repetitions	Sets	Exercise
Phase 1	Week 1–2	Easy-moderate	45 minutes *	8–10	2–3	Sit-to-stand, Shoulder press, Bicep curl, Calf raise
Phase 2	Week 3–5	Easy-hard	45–50 minutes *	10–12	3	Sit-to-stand, Shoulder press, Bicep curl, Calf raise
Phase 3	Week 6–8	Moderate-hard	60 minutes *	12	3	Sit-to-stand, Shoulder press, Bicep curl, Calf raise, Leg extension, Lateral arm raise
Phase 4	Week 9–12	Moderate-hard	60 minutes *	12	3	Sit-to-stand, Shoulder press, Bicep curl, Calf raise, Leg extension, Lateral arm raise

*Rest period is the same throughout the whole programme: 1–2 minutes between sets; 2–3 minutes between exercises and at least 48 hours between sessions

### Data collection

Initial screening data will be collected over the telephone, which will capture home care status, SARC-F score, MNA-short form score, and demographic data. Written informed consent will be obtained at the baseline assessment in the participant’s home (Appendix C)
^
45
^. Outcome data will be collected at baseline (T1), post-intervention (T2) and 12-weeks post-intervention (T3) in the participant’s home and will be recorded on an online form (Google Forms). If required, assistance with data collection will be provided by the participant’s home carer. Adherence to the ONS will be recorded post-intervention. Adherence to the RT programme will be monitored and recorded throughout the study intervention (T2) (
Table 3).

**Table 3. T3:** Measures at the three study timepoints.

TIMEPOINT	T1 Baseline	T2 Post-intervention	T3 12 weeks post- intervention
ENROLMENT			
Eligibility	☒		
Randomisation	☒		
Written informed consent	☒		
OUTCOMES			
Timed Up & Go	☒	☒	☒
Mini Nutritional Assessment-Full Form	☒	☒	☒
Body composition	☒	☒	☒
Dietary recall	☒	☒	☒
4-metre gait speed	☒	☒	☒
Handgrip strength	☒	☒	☒
Five times Sit-To-Stand	☒	☒	☒
Cognitive function	☒	☒	☒
Depression risk	☒	☒	☒
Activities of daily living	☒	☒	☒
Quality of life	☒	☒	☒
Number of participants recruited	☒		
Number of participants retained		☒	☒
Adherence to oral nutritional supplement		☒	
Adherence to resistance training		☒	
Acceptability of oral nutritional supplement		☒	
Acceptability of resistance training		☒	

### Study outcomes

**
*Primary outcomes*
**

The primary study outcomes are physical function, assessed using TUG
^
54
^ and nutritional status, determined using the MNA-FF
^
55
^.

**Timed Up and Go**

Participants will be timed when asked to stand up from a standardised armchair (46 cm seat height), walk 3 metres, turn around, walk back and sit down
^
54
^. The use of a walking aid will be permitted. The following reference values will be used: 9.2 (8.2–10.2) seconds for 70 to 79 years, and 11.3 (10–12.7) seconds for 80 to 99 years
^
56
^. A cut-off time of 20 seconds
^
1
^ or those unable to complete the TUG due to health problems will be considered low physical function
^
57
^. The TUG has demonstrated good inter-rater and intra-rater (intraclass correlation coefficient = 0.99) reliability
^
54
^.

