**Body composition**

Height will be measured with a stadiometer, with shoes removed. In participants who are unable to stand, height will be estimated by measuring ulna (forearm) length (cm) with reference to predictive equations
^
60
^. For ulna length, the distance between the olecranon process and the midpoint of the prominent bone of the wrist (styloid process) will be measured with the left arm folded across the chest with the fingers pointing towards the shoulder
^
60,
61
^.

Participants’ body composition [fat (kg/%), muscle (kg/%), and weight (kg) and BMI (kg/m
^2^)] will be assessed using the Tanita MC-780MA (2015, Tanita Corporation, Japan), an 8 electrode multi-frequency segmental body composition analyser
^
62,
63
^.

Calf and mid-upper arm (MUAC) circumferences will be measured. Calf circumference will be measured with a non-elastic measuring tape using the widest part of the calf
^
64
^. MUAC will be measured using the same tape, at the midpoint between the acromial process of the shoulder and the olecranon process of the elbow with the arm hanging relaxed at the participant’s side
^
65
^. Measurements will be taken while seated.

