### Statistical analysis plan

Statistical analyses will be performed using SPSS Statistics for Windows, version 27 (SPSS Inc., Chicago, Ill., USA) and RStudio (2023.06.2. Posit, PBC) as appropriate. Data cleaning will be conducted prior to analysis.

Demographic data and study primary and secondary outcomes will be described using measures such as mean and standard deviation, median and interquartile range, 95% confidence interval, or count and percentage. Descriptive statistics will also be used to report the feasibility of the intervention. Missing data will not be imputed for the primary analysis.

Data will be analysed using the intention-to-treat approach, wherein all participants who have been randomly allocated to the study intervention
^
80
^ will be included. The between-group and within-group difference at baseline (T1), post-intervention (T2) and 12-weeks post-intervention (T3) in primary and secondary outcomes will be analysed using either parametric or non-parametric, based on the normality of data distribution. The primary outcome is TUG and MNA-FF post-intervention (T2). Further, a mixed between-within linear model will be used to assess group, time, and group x time interaction effects. Between-group linear mixed-model analysis will be used to assess the mean difference in change from baseline to post-intervention. The dependent variables will be TUG and MNA-FF with group (ONS + RT, RT), time (baseline, post-intervention), and the group-by-time interaction as fixed factors; participant ID as a random factor; and baseline values as covariates. Effect sizes (partial eta squared) will be calculated using the Cohen’s d classification (0.01 = small, 0.06 = moderate, 0.14 = large). Variables not normally distributed will be transformed as appropriate. The proportion of participants whose TUG and/or MNA-FF improved or deteriorated post-intervention (T2) will be calculated. The interindividual variability in response to the ONS will be calculated using the Atkinson and Batterham formula
^
81
^.

Using the same approach as above, between-group differences and within-group differences at baseline (T1), post-intervention (T2), and 12 weeks post-intervention (T3) will be analysed for secondary outcomes.

A per-protocol analysis will also be conducted, including participants who adhered to the intervention and have baseline (T1) and post-intervention (T2) measurements
^
82
^.

A p-value of less than 0.05 will be considered statistically significant.

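### Inability to complete the TUG has no time or rank, so the primary TUG analysis either omits it or treats it as missing at random

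*Protocol article*

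**What the plan says.** All places are in the protocol article.

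- **Timed Up and Go.** The measure is a time: "Participants will be timed when asked to stand up from a standardised armchair (46 cm seat height), walk 3 metres" and back. Walking aids are allowed. After a 20-second cut-off the text continues "or those unable to complete the TUG due to health problems will be considered low physical function". No time, ceiling value or rank is given for these participants.
- **Statistical analysis plan, outcome and model.** TUG and MNA-FF at T2 are the primary outcomes. Groups are compared at each time point by parametric or non-parametric methods. A linear mixed model follows, with TUG itself as dependent variable, fixed effects for group, time and their interaction, a random participant effect, and the baseline value as covariate. The low-function category appears in no stated primary analysis.
- **Statistical analysis plan, missing data and population.** "Missing data will not be imputed for the primary analysis". The approach is intention-to-treat, "wherein all participants who have been randomly allocated to the study intervention" being included.
- **Statistical analysis plan, per-protocol set.** It requires both T1 and T2 measurements.
- **Table 1.** No exclusion is based on mobility.

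**The concern.** A participant who was visited at T2 and could not do the test has a known, poor outcome. The plan foresees this person and labels the result, but its primary analysis has nowhere to put it. With no value in seconds and no imputation, the result becomes a missing T2 time.

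That matters because the reason for the gap is the outcome itself. If more people become unable in one arm, that arm's mean time is taken over its better performers and looks faster than it should. The arm that declines more is favoured. With 23 per arm, one or two people carry visible weight. Neither participants nor researchers are blinded, so a decision on how to score inability made after the data are seen would be open to challenge.

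**Working it through.** **1. Which analyses lose what**

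| Participant | Simple T2 group test | Mixed model | Per-protocol |
|---|---|---|---|
| T1 time, unable at T2 | out | T1 row can stay if fitted by likelihood; T2 handled as missing at random | out |
| Unable at T1 | in only if timed at T2 | out: no baseline covariate | out |

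So the simple tests cannot include everyone randomised. The mixed model can keep the first kind of participant, but it predicts the missing T2 time as if inability carried no information beyond the data in the model.

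**2. The plan's own figure**

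The Sample size section gives 15 per group for a 3.7 s difference, 80% power and p<0.05, then raises this to 23 per group. The SD is not stated, so the 15 cannot be reproduced independently and was solved backwards. In a two-sided two-sample t test (noncentral t), 80% power at 15 per group needs a standardised difference of 1.06, so SD = 3.7/1.06 ≈ 3.49 s. Since 14 per group must fall short (standardised difference below 1.10), the SD lies between 3.36 and 3.49 s. A one-sided test would imply 3.83 to 3.98 s. Sidedness is not stated; two-sided is assumed below. With SD 3.49 s, power at 23 per group is 0.94.

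**3. Loss unrelated to outcome**

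If equal numbers per arm lack a T2 time for reasons unrelated to function, only power is affected: 0.92 with 2 lost per arm, 0.89 with 4, and 0.80 with 8 (leaving 15). This case is benign.

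**4. Loss of the slowest from one arm**

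Assumptions: normal times, SD 3.49 s, 23 per arm, the slowest k in RT-only have no T2 time, none lost in ONS + RT, t test at T2, 20,000 simulated trials.

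| k lost | Estimate when truth is 3.7 s | Shift | Shift/3.7 | Power | Rejection rate when truth is 0 |
|---|---|---|---|---|---|
| 0 | 3.7 s | 0 | 0% | 0.94 | 0.05 |
| 1 | 3.4 s | 0.32 s | 9% | 0.90 | 0.07 |
| 2 | 3.1 s | 0.56 s | 15% | 0.86 | 0.10 |
| 3 | 2.9 s | 0.81 s | 22% | 0.80 | 0.14 |
| 4 | 2.7 s | 1.04 s | 28% | 0.73 | 0.19 |

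If the two are lost from ONS + RT instead, the same shift adds to the apparent benefit: 3.7 + 0.56 = 4.26 s. The last column is conditional on the uneven split; it is not the trial's overall type I error. If 2 are lost from each arm, the estimate stays at 3.7 s, with a rejection rate under no difference of about 0.075.

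**5. Worst-rank scoring**

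With 2 versus 0 unable and those two given the worst rank, a Mann-Whitney test (4,000 trials, no other missing data) keeps all 46 in the comparison, with power of about 0.93, the same as with nobody unable. If inability is equal in both arms, it costs some power: 0.91 with 2 per arm and 0.85 with 4.

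**The case against.** The strongest reply is that the mixed model does not delete people. Time is a factor with baseline as one level, so a likelihood fit can retain a participant with a T1 time and no T2 time, and leaving values unimputed is normal in such a model. This stands. A reader might infer that everyone unable at T2 vanishes from the primary analysis; the documents do not support that. What remains is the doubtful missing-at-random assumption, the complete-case T2 tests, and the loss of anyone unable at T1.

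Second, how inability is coded and which sensitivity analyses are run are often left to an analysis plan, and none is shown. That is fair for the detail. But the article itself fixes the label without a value, the bar on imputation, and the claim that all randomised are included, and these do not fit together.

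Third, inability may be rare. Every phase in Table 2 includes sit-to-stand, though exercises can be modified; people advised by their GP not to exercise are excluded; and walking aids are allowed. The Body composition section does provide for some who cannot stand ("In participants who are unable to stand, height will be estimated"), but that is a fallback for height and says nothing about TUG frequency. No rate can be drawn from the documents.

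Fourth, a reader might infer a very large bias. Assigning 30 s to three people in one arm, with the other 20 averaging 11.3 s, shifts that arm's mean by 3 × (30 − 11.3)/23 = 2.44 s, or 66% of 3.7 s. That needs 3 versus 0 unable, and it uses the reference value for ages 80 to 99 as the mean of a home-care group. With SD 3.49 s, 30 s lies (30 − 11.3)/3.49 ≈ 5.4 SD above that mean. Even so, 2.44 s is below 3.7 s, so a reversal of the planned difference is not shown.

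Last, speaking of intention-to-treat with some outcomes missing is ordinary usage. That is so, and a short qualification settles it.

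**Conclusion.** The point holds in a limited form. For the TUG primary outcome (MNA-FF is not affected), the article foresees an observed poor result, gives it no place on the analysed scale, and still states that all randomised participants are included. Followed as written, that result is absent from the simple T2 comparisons and enters the mixed model only under an implausible missing-at-random assumption. A participant unable at T1 is outside the TUG model.

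The size is unknown because no inability rate is given. Under the stated assumptions, 2 versus 0 unable shifts the T2 difference by about 0.6 s, about 15% of the target, with a conditional false-positive rate of about 0.10. The sign depends on which arm loses more. These figures are for an unadjusted T2 t test; the mixed model was not simulated. This should be corrected, but it does not invalidate the design.

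**What to change.** 1. Record inability for health reasons separately from a test not done for other reasons, at T1, T2 and T3, if the data form (not shown) does not already do so.
2. Keep the seconds-scale model as the primary estimate.
3. Prespecify one supportive rank-based comparison of T2 TUG in which those unable for health reasons share the worst rank. Report it beside the primary estimate. It should not be a second success criterion: requiring both to succeed would change the decision rule and could only keep or lower power.
4. Reword the intention-to-treat sentence along these lines: *Participants are analysed in the arm to which they were randomised, using available data. Those unable to complete the TUG for health reasons at T2 have no time in the seconds-scale model and take the worst rank in the supportive analysis.* Add a clause on how those unable at T1 enter each analysis.

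Settle this before outcomes are compared by arm. The cost is one recorded item if it is not already there, one extra analysis and a few sentences. The small downside is that the rank result is not in seconds.

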**Mini-Nutritional Assessment-Full Form**

The MNA-FF will be used to assess the nutritional status of participants. The MNA-FF includes 18 questions to assess an individual’s nutritional status
^
55
^. The MNA-FF includes anthropometric measures and questions on general health status, dietary habits and self-perceived health and nutrition status
^
58
^. A score of 24–30 indicates that an individual is normally nourished, 17–23.5 that an individual is at risk for malnutrition, and a score of <17 that the person is malnourished
^
55
^. The MNA-FF has demonstrated high sensitivity (96%), specificity (98%), and predictive value (97%) in accurately identifying the nutritional status of older adults compared to clinical assessment
^
59
^.

**
*Secondary outcomes*
**

**Body composition**

Height will be measured with a stadiometer, with shoes removed. In participants who are unable to stand, height will be estimated by measuring ulna (forearm) length (cm) with reference to predictive equations
^
60
^. For ulna length, the distance between the olecranon process and the midpoint of the prominent bone of the wrist (styloid process) will be measured with the left arm folded across the chest with the fingers pointing towards the shoulder
^
60,
61
^.

Participants’ body composition [fat (kg/%), muscle (kg/%), and weight (kg) and BMI (kg/m
^2^)] will be assessed using the Tanita MC-780MA (2015, Tanita Corporation, Japan), an 8 electrode multi-frequency segmental body composition analyser
^
62,
63
^.

Calf and mid-upper arm (MUAC) circumferences will be measured. Calf circumference will be measured with a non-elastic measuring tape using the widest part of the calf
^
64
^. MUAC will be measured using the same tape, at the midpoint between the acromial process of the shoulder and the olecranon process of the elbow with the arm hanging relaxed at the participant’s side
^
65
^. Measurements will be taken while seated.

**Dietary intake**

A 24-hour dietary recall using a multiple pass technique will be conducted at each home-based assessment to establish the dietary pattern of each participant
^
66
^. Participants will be asked to recall all foods and drinks consumed in the previous 24 hours, commencing with first intake of food or drink of the day. Any dietary supplement(s) consumed will also be recorded. The list of foods will be repeated back to the participant, and using closed questions, each participant will be asked about foods frequently omitted (e.g., sauces, dressings, beverages, sweeteners, etc.), timing of meals and additional snacks. A detailed description of food consumed (type, brand, weight) will be recorded. The dietary intake data will be reviewed for a third time with the participant to validate the information. The 24-hour dietary recall data will be analysed using Nutritics
^TM^ software (version 5.96). Intakes of protein (g) and energy (kilocalorie) will be calculated as g/kgBW and as kilocalorie/kgBW respectively. Changes in macro and micronutrient intakes between all three timepoints will be assessed.

